### Randomization

Randomization, achieved using the Clinsight® software, will take place within 15 days of the initiation of the targeted therapy. Patients will be allocated to either the experimental SPEP group or the recommended adapted physical activity group in a ratio 2:1. Randomization will be stratified per site, baseline level of fatigue, targeted therapy, number of lines of prior therapy in the metastatic status, and age.

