### Statistical plan

#### Sample size

The primary objective for the phase II is the feasibility of the study. The SPEP participation will be considered sufficient if a patient has performed at least 50% of the theoretically planned sessions within 3 months (supervised and non-supervised). With a unilateral alpha risk of 5%, a statistical power of 85%, a probability of inefficiency maximum of 50%, a probability of minimum efficiency of 65%, and a 5% lost to follow-up rate, 120 patients will need to be randomized in the phase II with a 2:1 ratio (74 patients in the SPEP; 37 patients in the control arm of recommended adapted physical activity). Patients will be included in a non-competitive manner in the different cohorts. An interim analysis is planned when 37 patients will be randomized in the SPEP arm with rejection of H0 if at least 27 patients have completed at least 50% of the planned sessions; rejection of H1 (futility) if 19 patients or less have completed at least 50% of the planned sessions.

The phase III study will evaluate the 3-month efficacy of the SPEP, compared to recommended adapted physical activity. The 120 patients randomized in the phase II will be included in the phase III analysis. The co-primary endpoint criteria are the fatigue score (using FACT-F) and the physical well-being score (using FACT-G) evaluated after 3 months. SPEP superiority over the recommended adapted physical activity program will be demonstrated if at least one of the criteria (FACT-F or FACT-G) increase significantly without deterioration of other criteria. To demonstrate a clinically significant difference of at least 5 points (standard deviation: 13) for the physical well-being dimension of the FACT-G questionnaire and at least 2.5 points (standard deviation: 6.5) for FACT-F questionnaire at 3 months [17, 18], with a bilateral alpha risk of 2.5%, a statistical power of 80%, and a 5% lost to follow-up rate, 312 patients will need to be randomized in the phase III. The inclusions will be non-competitive between the 4 cohorts (78 patients per cohort). A 30-month inclusion period is predicted for the recruitment of these 312 patients in 18 French centers. An interim analysis is planned at the end of the phase III corresponding to 39.5% of patients randomized in order to reject H0 or H1 according to alpha spending function.

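### The co-primary t-test ignores the five stratification factors, tumour cohort and baseline score; sparse strata may leave chance imbalance that only an adjusted analysis would recover

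*Protocol article*

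**What the plan says.** The Randomization section names five factors: "Randomization will be stratified per site, baseline level of fatigue, targeted therapy, number of lines of prior therapy in the metastatic status, and age". It also sets the ratio: "Patients will be allocated to either the experimental SPEP group or the recommended adapted physical activity group in a ratio 2:1". It gives no factor levels, block size or allocation algorithm.

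The Sample size section gives the scale: "A 30-month inclusion period is predicted for the recruitment of these 312 patients in 18 French centers". The phase II patients are part of that total: "The 120 patients randomized in the phase II will be included in the phase III analysis". Recruitment is organised by four tumour cohorts with a quota of 78 each. The quota fixes each cohort's total, not its split between arms, and cohort is not among the stratification factors.

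The Statistical analysis section makes the co-primary comparison a t-test of the 3-month FACT-F and physical well-being scores by arm, at the 2.5% level. A repeated-measures analysis of variance that takes the baseline score into account is listed as an additional analysis. Univariate and multivariate models then look for factors associated with change.

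**The concern.** Five factors including site give about as many cells as patients. If each cell has its own block list, most lists are never completed, and the balance that stratification is meant to secure is only partly delivered. Tumour cohort, which shapes the whole recruitment plan, is not balanced by design. The Background reports fatigue in 90% of renal cancer patients on antiangiogenic tyrosine-kinase inhibitors and 60% of breast cancer patients on everolimus, so fatigue plausibly differs between tumour and drug groups.

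An adjusted analysis would make either problem largely harmless, but the co-primary test is unadjusted. If the factors are well balanced, the t-test ignores that balance and its standard error is too large. If they are not, chance imbalance stays in the estimate. At stake is the precision of the comparison on which the phase III conclusion rests.

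**Working it through.** **Inputs.** 312 patients, 18 centres, four cohorts of 78, and the sample-size assumptions (Sample size); 2:1 ratio and five factors (Randomization). The effect assumptions are a 5-point difference with SD 13 for physical well-being, and "at least 2.5 points (standard deviation: 6.5) for FACT-F questionnaire at 3 months".

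**The plan's own figure.** Both endpoints have a standardised effect of 5/13 = 2.5/6.5 = 0.385. With two-sided alpha 2.5%, 80% power and 2:1 allocation, the standard two-mean formula gives 97 + 194 = 291. Dividing by 0.95 gives 307, close to the stated 312. The calculation therefore uses the full outcome SD and takes no credit for baseline information.

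**Cells.** Every factor needs at least two levels.
- Two levels for each non-site factor: 18 x 2^4 = 288 cells; 312/288 = 1.08 patients per cell. This is the most favourable case.
- Four therapy groups (assumed): 576 cells, 0.54 per cell.
- Seven therapy groups (the classes named under Oral targeted therapies): 1008 cells, 0.31 per cell.
- Phase II alone: 120/288 = 0.42 per cell.
- Site dropped, all others binary: 16 cells, 19.5 per cell.

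With 288 equal cells and Poisson counts of mean 1.08, about 34% are empty, 37% hold one patient, and about 10% reach three, the smallest complete 2:1 block.

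**Balance on baseline fatigue.** The measure is the SD of the between-arm difference in the share with high fatigue, assuming 50% high, independent factors and equal-sized sites. Under simple randomisation the formula gives 0.5 x sqrt(1/208 + 1/104) = 6.0 points; one simulation gave 6.3. Simulated values for the alternatives:

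| Method | SD, points |
|---|---|
| Blocks of 3, 288 cells | 4.4 |
| Blocks of 3, 576 cells | 5.2 |
| Blocks of 6, 288 cells | 5.5 |
| Blocks of 6, 576 cells | 5.7 |
| Blocks of 3, 16 cells (no site) | 1.1 |
| Minimisation on the five factors | 1.0 |

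Against 6.0, cross-classified blocks cut imbalance by between 5% (1 - 5.7/6.0) and 27% (1 - 4.4/6.0). Against the simulated 6.3 the range is about 9% to 30%. Unequal site sizes improve this somewhat: with 1/rank sizes the four block designs gave 4.1 to 5.3.

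**Balance within cohort.** If cohort is independent of the factors, the SPEP count among 78 has mean 52 and SD sqrt(78 x 2/3 x 1/3) = 4.2, so a 95% range of about 44 to 60. The SD of the between-arm difference in one cohort's share was about 5 points under every method simulated, including minimisation on the five listed factors. If therapy group coincided with cohort, blocks of 3 narrow the range only to about 45 to 59.

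**Cost of the unadjusted test.** Assume the baseline FACT-F SD equals the stated 6.5. Under simple 2:1 randomisation of 312, the between-arm difference in mean baseline score has SD 6.5 x sqrt(1/208 + 1/104) = 0.78 points, or about +/-1.5 at 95%, against a target effect of 2.5. For a baseline-to-3-month correlation r, adjusting for the baseline score removes r^2 of the outcome variance and multiplies the standard error by sqrt(1 - r^2):
- r = 0.3: 9% removed; factor sqrt(0.91) = 0.95.
- r = 0.5: 25% removed; factor sqrt(0.75) = 0.87.
- r = 0.7: 49% removed; factor sqrt(0.51) = 0.71.

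The documents give no correlation, so this range is an assumption.

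**The case against.** The strongest reply is that the article never says permuted blocks are used within cross-classified cells. The word stratified is often applied to minimisation, and the algorithm is the kind of detail an article leaves to the full protocol. Minimisation on the same five factors brings the fatigue SD down to about 1.0 point. This stands. A reader might infer from the cell count that stratification barely protects balance, or that allocation amounts to simple randomisation. The documents do not support that: it needs an unstated algorithm, and even blocks of 3 cut imbalance by roughly 13% to 30%, depending on the number of cells and the benchmark.

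Second, targeted therapy is a factor and is linked to tumour type; the Background itself pairs drugs with tumours. So the split within a cohort is not wholly left to chance. This also stands, although the grouping of therapies is not given and the simulated gain under sparse blocks is small.

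Third, chance imbalance under randomisation does not bias the t-test or inflate its type I error. This is correct, and a reading that the comparison would be invalid should be rejected.

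Fourth, a baseline-adjusted analysis is already planned. It is, but as an addition to the co-primary t-test. The multivariate models are aimed at finding factors associated with change and admit covariates by univariate p < 0.1, so they do not replace a prespecified adjusted treatment comparison.

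**Conclusion.** The point holds as a matter of efficiency. The counts are firm: at least 288 cells, at most 1.08 patients per cell, and tumour cohort not listed as a factor. Weak balance is conditional on cross-classified blocks, and the size of the weakness depends on assumed levels, block sizes and site sizes.

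What does not depend on the algorithm is the analysis. The co-primary t-test discards the baseline score, the randomisation factors and cohort. The cost is precision: an estimated 9% to 49% of outcome variance from the baseline score alone, for an assumed correlation of 0.3 to 0.7. One might conclude that the randomisation system has to be rebuilt. That does not follow: the algorithm may already be adequate, and a change during recruitment would put two allocation schemes into one confirmatory analysis.

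**What to change.** Replace the co-primary t-test with a linear model (ANCOVA) of each 3-month score on arm, adjusted for the matching baseline score, tumour cohort, targeted-therapy class, number of prior metastatic lines and age. In the physical well-being model, also include baseline fatigue level, since it is a randomisation factor. Treat site as a random effect or omit it, given about 17 patients per centre (312/18). Keep the 2.5% level for each endpoint and retain the t-test as a sensitivity analysis. Fix the covariate coding before any comparative data are seen, including the planned phase III interim analysis.

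The cost is wording in the analysis plan. FACT-F and FACT-G are already collected at baseline, and the phase III analysis population already requires both baseline scores. The sample size need not change, because it was computed without credit for adjustment. No change to the randomisation system is required.

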## Discussion

One of the most significant advance in the treatment of cancer in the past few decades has been the introduction of targeted therapies. Compare to chemotherapeutic drugs, OTT are more convenient (with some oral routes) and precise. However, OTT induce specific side effects, and fatigue is one of the most important early side effect reported by patients. This fatigue causes significant impairment in QoL and may also be a predictor of shorter survival in cancer patients [12]. Some reports suggested that fatigue related to cancer treatments differs from, and is more debilitation than normal fatigue induced by other causes such as sleep disturbance and exercise. Furthermore, patients described fatigue related to cancer treatments as unusual, excessive, unrelated to activity, and not relieved by sleep or rest [19]. Cancer-related fatigue is multi-dimensional and may have physical, mental, and emotional manifestations including generalized weakness, diminished concentration or attention, decreased motivation or interest to engage in usual activities, and emotional lability [20].

This present article describes the QUALIOR study protocol of a randomized controlled trial of a home-based SPEP for metastatic cancer patients treated with oral targeted therapies. The originality of our study lies on the presence of a personal coach for a supervised home-based and well-designed standardized physical exercise program for the management of advanced cancer patients treated with OTT. The first part of the study (phase II) is designed to evaluate the feasibility of the home-based SPEP in this group of metastatic cancer patients who are particularly frail. The second part of the study (phase III) aims to demonstrate that supervised physical exercise may help these patients to minimize the OTT-related fatigue and improve their QoL. We expect that the SPEP will prove a positive impact on patient fatigue and quality of life compared to the recommended adapted physical activity. Secondary endpoints will explore if SPEP may improve patient survival along with a decrease of OTT toxicity. Most of the parameters studied in this trial will be evaluated using approved French versions of commonly used self-assessment questionnaires.

Cancer treatment-related fatigue may lead to poor adherence to treatment and is often a reason for patients’ treatment discontinuation. Cancer treatment adherence is crucial to obtain optimal health outcomes. Cancer treatment non-adherence leads to high treatment failure and decreased survival [21]. The design of the QUALIOR study will allow to investigate if the SPEP-decreased OTT-related fatigue may improve OTT adherence, and increase patient survival (progression-free and overall survival).

Apart from the fact that treatment-related fatigue causes significant impairment in overall quality of life during treatment, has a negative impact on social relationships, mood, daily activities, and patient survival [22], it also has negative influence on work abilities and by consequence an important economic implications. These economic impacts not only involve patients but also caregivers who often need to reduce work hours, accept fewer responsibilities, take days off, or ultimately stop working [23]. Furthermore, treatment-related fatigue has a cost for the society and the health care system [21]. For these reason, an ancillary research of the QUALIOR study will assess the economic impact of the SPEP compare to the recommended adapted physical activity.

In conclusion, the QUALIOR study aim to answer whether or not supervised physical exercise program at home is feasible among a group of metastatic cancer patients treated with oral targeted therapy and may decrease fatigue, the major side effect observed for these patients, resulting in an improved drug efficacy and patients’ quality of life.

## Trial status

Recruitment began 11 July 2017 and is still ongoing at the date of publication.

## Data Availability

Not applicable

## Abbreviations

A/CS: Anorexia/cachexia subscale
ALAT: Alanine transaminase
ASAT: Aspartate transaminase
ALP: Alkaline phosphatase
aPTT: Partial thromboplastin time
C: Checkup
Ca: Calcium
CBC: Complete blood count
E: Evaluation
ECOG: Eastern Cooperative Oncology Group
EGFR: Epidermal growth factor receptor
EQ-5D-3L: EuroQol-5 dimensions-3 levels
FAACT: Functional assessment of anorexia/cachexia therapy
FACT-Cog: Functional assessment of cancer therapy-cognitive
FACT-F: Functional assessment of cancer therapy-fatigue
FACT-G: Functional assessment of cancer therapy-general
γGT: Gamma glutamyl transpeptidase
HADS: Hospital anxiety and depression scale
HDL: High-density lipoprotein
IPAQ: International physical activity questionnaire
ITT: Intention-to-treat
K: Potassium
LDL: Low-density lipoprotein
M: Month
mITT: modified intention-to-treat
MRI: Magnetic resonance imaging
Na: Sodium
NCI-CTCAE: National cancer institute - common terminology criteria for adverse events
OTT: Oral targeted therapy
PARP: Poly(ADP-ribose) polymerase
PT/INR: Prothrombin time and international normalized ratio
QoL: Quality of life
SCAT: Sub-cutaneous adipose tissue
SPEP: Supervised physical exercise program
T4: Thyroxine
TAP-CT: Computed tomography of thorax, abdomen and pelvis
TP: Prothrombin
TSH: Thyroid-stimulating hormone
VAS: Visual analogue scale
VAT: Visceral adipose tissue
